### 3.3. PHASE II TRIALS

Patients with advanced or metastatic solid tumors will be included in 10 independent single-arm open-label phase II trials:

- [A] Colorectal cancer not MSI-H or MMR-deficient (standard dose)
- [B] GIST
- [C] Oesophageal or gastric carcinoma
- [D] Biliary tract cancer, hepatocellular carcinoma
- [E] Soft Tissue Sarcoma (STS)
- [F] Radioiodine-Refractory Differentiated Thyroid Cancer (RR-DTC)
- [G] Neuroendocrine gastroenteropancreatic tumors (GEP-NETs).

The design of these single-arm phase II trials will follow an adaptative trial design (Bayesian approach, Section 10 for statistical considerations).

The administered dose of Regorafenib will be the RP2D defined in the dose escalation part of the trial (see above).

- [H] Non-small cell lung cancer (NSCLC)
- [I] Solid tumors (including soft Tissue Sarcoma) with immune signature (TLS+).

The design of these single-arm phase II trials will follow an optimal two-stage Simon's design (see section 10 for statistical considerations).

The administered dose of Regorafenib will be the RP2D defined in the dose escalation part of the trial (see above).

- [A'] Colorectal cancer not MSI-H or MMR-deficient with immune signature (based on low tumor-associated macrophages infiltrate level).

The design of this single-arm phase II trial will follow an optimal two-stage Simon's design (see section 10 for statistical considerations).

The administered dose of Regorafenib will be at a fixed low-dose of 80 mg/day.

- [J]: Urothelial cancer
- [K]: HPV-associated cancer
- [L]: Triple negative breast cancer
- [M]: TMB-high solid tumors
- [N]: MSI-high solid tumors
- [O]: Non clear-cell renal carcinoma
- [P]: Malignant pleural mesothelioma.

The design of these single-arm phase II trials will follow an exact single-stage A'Hern design.

The administered dose of Regorafenib will be the RP2D defined in the dose escalation part of the trial.

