### 7.6.2. Management of Adverse Events

Any toxicity observed during the course of the study could be managed by interruption and/ or dose reduction of the dose if deemed appropriate by the Investigator. Dose adjustments are to be made according to the greatest degree of toxicity (please refer to the IMP Investigator's Brochure), and in accordance with table below:

| Level       | -1        | 1          | 2          |
|-------------|-----------|------------|------------|
| Avelumab    | 10 mg/kg  | 10 mg/kg   | 10 mg/kg   |
| Regorafenib | 80 mg x 1 | 120 mg x 1 | 160 mg x 1 |

Adverse events will be graded using the NCI Common Terminology Criteria for Adverse Events Version (CTCAE) v5.0.

The following guidelines outline dose adjustments for the most frequent of these toxic effects. If any severe toxicity occurs it should be referred to the principal investigator in order to decide management in the best interest of the patient. If a patient experiences several adverse events with conflicting recommendations, please use the dose modification recommendation that reduces the dose to the lowest level.

Once a dose has been reduced, it will in no case be increased again.

For all cohorts except cohort [A'], patients requiring a delay of > 4 weeks OR > one dose reduction (of Regorafenib) if RP2D is 120mg of Regorafenib and > 2 dose reductions if RP2D is 160mg of Regorafenib should permanently discontinue regorafenib. Note that further treatment by avelumab monotherapy will be allowed until disease progression, unacceptable toxicity, etc. (see section 3.2.2 for more details).

For cohort [A'], regorafenib should be interrupted and no dose reduction are allowed. Patients requiring a delay of > 4 weeks should permanently discontinue regorafenib. Note that further treatment by avelumab monotherapy will be allowed until disease progression, unacceptable toxicity, etc. (see section 3.2.2 for more details).

Patient should go off study if regorafenib has been permanently discontinued before first dose of avelumab.

Please refer to Appendix 7 and 8 and to most updated Investigator Brochure for management of toxicities.

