## APPENDIX 7: DOSE MODIFICATION/DELAY FOR TOXICITIES RELATED TO REGORAFENIB (EXCEPT FOR HAND-FOOT SYNDROME REACTION, HYPERTENSION, AND ALT AND/OR AST AND/OR BILIRUBIN INCREASES)

| NCI-CTCAE v5.0 | Dose interruption                       | Dose modification c                                                                             | Dose for subsequent cycles      |
|----------------|-----------------------------------------|------------------------------------------------------------------------------------------------------------|---------------------------------|
| Grade 0-2      | Treat on time                           | No change                                                                                                  | No change                       |
| Grade 3        | Delay until $\leq$ grade 2 a | Reduce 1 dose level                                                                                        | No possibility of re-escalation |
| Grade 4        | Delay until $\leq$ grade 2 b | Reduce 1 dose level
Permanent discontinuation must be discussed with the sponsor in case of recurrence. |                                 |

a- Excludes alopecia, non-refractory nausea/vomiting, non-refractory hypersensitivity and asymptomatic laboratory abnormalities

b- If no recovery after a 4 weeks delay, treatment will be permanently discontinued.

c For cohort [A], regorafenib should be interrupted and no dose reduction are allowed. Patients requiring a delay of > 4 weeks should permanently discontinue regorafenib.

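### As the text reads, six of the nine no-dose-reduction footnotes in Appendices 7 and 8 name cohort A (160 mg), whereas section 7.6.2 and the other three footnotes name cohort A' (80 mg)

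*Protocol*

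**What the plan says.** Protocol section 7.6.2 states the rule from both sides. For the low-dose colorectal cohort it says: "For cohort [A'], regorafenib should be interrupted and no dose reduction are allowed". For everyone else it sets limits on delay and reduction that open with "For all cohorts except cohort [A'], patients requiring a delay of > 4 weeks OR > one dose reduction", that figure applying if the RP2D is 120 mg. At the higher RP2D, patients with "> 2 dose reductions if RP2D is 160mg of Regorafenib should permanently discontinue regorafenib". Section 7.3 gives the phase II dose as 160 mg for all cohorts except A', so cohort A may have two reductions. Section 3.3 says of A': "The administered dose of Regorafenib will be at a fixed low-dose of 80 mg/day".

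Section 7.6.2 then sends sites to the toxicity tables: "Please refer to Appendix 7 and 8 and to most updated Investigator Brochure for management of toxicities". Nine of those tables carry a footnote repeating the no-reduction rule. In Appendix 7 (footnote c) and five of the eight footnotes in Appendix 8 it reads: "For cohort [A], regorafenib should be interrupted and no dose reduction are allowed". In the other three it carries the A' label, as section 7.6.2 does.

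**The concern.** Cohorts A and A' are both colorectal, differ by one mark in their label, and start at opposite ends of the dose range. A footnote that names the wrong one moves a dosing prohibition from the cohort that has no lower level to the cohort that has two.

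The tables are an operative instruction, because section 7.6.2 directs sites to them. A site using only the table for the event in front of it would find, under six of the nine footnotes, that a cohort A patient on 160 mg may be interrupted but not stepped down. Two of those six cover hand-foot skin reaction and hypertension, which section 1.2.3 lists as the most frequent drug-related events with regorafenib (56% and 48%). The same six tables, read literally, carry no exemption for A', whose patients would fall under a plain instruction to reduce one level.

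**Working it through.** No calculation is involved. The check sets the nine footnotes beside section 7.6.2 and the dose tables.

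**Doses.** Sections 3.2.3 and 7.6.2 define three regorafenib levels: 80 mg (level -1), 120 mg (level 1) and 160 mg (level 2). Cohort A starts at 160 mg (section 7.3), so its two permitted reductions are 160 to 120 mg and 120 to 80 mg. Cohort A' starts at 80 mg (sections 3.3 and 7.3), so it has no defined lower level.

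**Footnotes, in document order.**

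| Table | Cohort named | Agrees with section 7.6.2 |
|---|---|---|
| Appendix 7, general regorafenib toxicity | A | no |
| Appendix 8, hand-foot skin reactions | A | no |
| Appendix 8, hypertension | A | no |
| Appendix 8, ALT/AST/bilirubin | A | no |
| Appendix 8, diarrhoea/colitis | A' | yes |
| Appendix 8, rash | A | no |
| Appendix 8, endocrine disorder | A | no |
| Appendix 8, creatinine increased | A' | yes |
| Appendix 8, other immune-related events | A' | yes |

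Count: 6 name A, 3 name A', total 9. The pneumonitis and myocarditis tables contain no step-down and carry no such footnote.

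**Consequences of the literal reading.**

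1. Cohort A: the six tables allow only interruption, then resumption at the same dose or discontinuation. Section 7.6.2 allows two step-downs for the same events.
2. Within Appendix 8, a cohort A patient with Grade 3 rash could not be reduced, while the same patient with Grade 3 diarrhoea would be reduced one level. No reason is given for the difference.
3. Cohort A': the missing exemption has little effect, because section 7.6.2 bars reduction there and 80 mg is already the lowest level.
4. The limit of four weeks' delay is the same for both cohorts in section 7.6.2, so that half of the footnote does no harm under either label.

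**After correction.** If the six are read as A', all nine footnotes agree with section 7.6.2 and with each other.

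**The case against.** The strongest reply is that the protocol may contain no error. The text was read from a PDF by a program, and a prime in small footnote print is easily lost. The footnotes repeat the section 7.6.2 sentence almost word for word, including its grammatical slip, which suggests one sentence pasted nine times from a source that had the prime. The label then alternates with no clinical or drafting logic, as sporadic loss of a small mark would produce. This stands as a reason for caution, and it cannot be settled from the text.

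It does not dispose of the point. The prime survived in three footnotes of the same appendix, in the same sentence. Outside the two appendices the 80 mg cohort is named with its prime throughout, including the bracketed mentions in sections 3.3 and 7.6.2. Those are body, heading and contents text rather than footnotes, so they make an artefact less likely without ruling it out.

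The second reply is that the meaning is clear even if A is printed: section 7.6.2 is explicit, three footnotes agree with it, and the rule makes sense only for a cohort already at the lowest dose. That stands too, and it keeps the point minor.

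A reader might infer that the appendices cancel dose reduction in cohort A. The documents do not support that. Section 7.6.2 still permits it and says toxicity may be "managed by interruption and/ or dose reduction of the dose if deemed appropriate by the Investigator". A reader might also count the step-down instructions under the six footnotes as a measure of harm. Such a count would be of table cells, some of them conditional: the hypertension step applies only if blood pressure stays uncontrolled, and the liver step only if benefit is judged to outweigh risk. It would measure neither patients nor risk.

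**Conclusion.** As the text reads, the protocol contradicts itself on a dosing rule: six of nine footnotes place the ban on reduction on cohort A, and section 7.6.2 with the other three footnotes places it on cohort A'. Severity is minor. The intended reading is A', the conflict can be resolved from section 7.6.2, and no sample size, error rate or efficacy analysis is affected. The number of patients who might be managed differently is unknown.

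Confidence is low to medium. The conclusion rests on one assumption, that the source PDF prints A in those six footnotes. If it prints A', the point falls. It would therefore be too strong to treat this as an established error in the plan.

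**What to change.** Look at the nine footnotes in the source PDF. If all print A', no change is needed. If any of the six (Appendix 7 general toxicity; Appendix 8 hand-foot, hypertension, liver, rash, endocrine) print A, change them to A' so that all nine match section 7.6.2, and send sites a short note. Sites should be told only once the error is confirmed. The cost is a brief check and, if needed, one character in up to six footnotes plus a letter.

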## APPENDIX 8: DOSE DELAYS FOR TOXICITIES RELATED TO AVELUMAB AND REGORAFENIB INCLUDED IMMUNE-RELATED TOXICITIES

| Hand-foot skin reactions
Except for irAE skin reaction                                                                                                                                         | Regorafeniba
Management/Dose-modification                                                                                                                                                                                                                                                                                                                                                                                                               | Avelumab
Management/Dose-modification |
|----------------------------------------------------------------------------------------------------------------------------------------------------------------------------------------------------------|------------------------------------------------------------------------------------------------------------------------------------------------------------------------------------------------------------------------------------------------------------------------------------------------------------------------------------------------------------------------------------------------------------------------------------------------------------------------------|-------------------------------------------------|
| Grade 1: Numbness, dysesthesia, paraesthesia, tingling, painless swelling, erythema or discomfort of the hands or feet which does not disrupt the patient's normal activities.                    | Any: Maintain dose level and immediately institute supportive measures for symptomatic relief.                                                                                                                                                                                                                                                                                                                                                                        | No dose modification                            |
| Grade 2: Painful erythema and swelling of the hands or feet and/or discomfort which affects the patient's normal activities.                                                                      | 1st occurrence:
Consider decreasing dose by one dose level and immediately institute supportive measures. If there is no improvement, interrupt therapy for a minimum of 7 days, until toxicity resolves to Grade 0-1.

No improvement within 7 days or
2nd occurrence:
Interrupt therapy until toxicity resolves to Grade 0-1. When resume treatment, treat at reduced dose level

3th occurrence:
Discontinue therapy. | No dose modification                            |
| Grade 3: Moist desquamation, ulceration, blistering or severe pain of the hands or feet, or severe discomfort that causes the patient to be unable to work or perform activities of daily living. | 1st occurrence:
Institute support measures immediately. Interrupt therapy for a minimum of 7 days until toxicity resolves to Grade 0-1. When resume treatment, decrease dose by one dose level

2nd occurrence:
Discontinue therapy                                                                                                                                                                                                                | No dose modification                            |

a For cohort [A], regorafenib should be interrupted and no dose reduction are allowed. Patients requiring a delay of > 4 weeks should permanently discontinue regorafenib

| Hypertension                                                                                                                                                 | Regorafeniba
Management/Dose-modification                                                                                                                                                                                                                                                                                                                                                                                                                                                                                                                                                                                | Avelumab
Management/Dose-modification                                                                                                             |
|---------------------------------------------------------------------------------------------------------------------------------------------------------------------|-----------------------------------------------------------------------------------------------------------------------------------------------------------------------------------------------------------------------------------------------------------------------------------------------------------------------------------------------------------------------------------------------------------------------------------------------------------------------------------------------------------------------------------------------------------------------------------------------------------------------------------------------|-------------------------------------------------------------------------------------------------------------------------------------------------------------|
| Grade 1 : Pre-hypertension (systolic BP 120-139 mmHg or diastolic BP 80-89 mmHg)                                                                             | Continue treatment
Consider increased blood pressure monitoring
No Anti-hypertensive therapy                                                                                                                                                                                                                                                                                                                                                                                                                                                                                                                                            | No dose modification                                                                                                                                        |
| Grade 2 : Systolic BP 140-159 mmHg or diastolic BP 90-99 mmHg
OR
Symptomatic increase by $\geq 20$ mmHg (diastolic) if previously within normal limits | Continue treatment.
If symptomatic, hold treatment until symptoms resolve AND diastolic BP $\leq 90$ mmHg. When treatment is restarted, continue at the same dose level.

Anti-hypertensive therapy : Treat with the aim to achieve diastolic BP $\leq 90$ mmHg:
- If BP previously within normal limits, start anti-hypertensive monotherapy
- If patient already on anti-hypertensive medication, titrate up the dose                                                                                                                                                                                                        | No dose modification                                                                                                                                        |
| Grade 3 : Systolic BP $\geq 160$ mmHg or diastolic BP $\geq 100$ mmHg
OR
More than one drug or more intensive therapy than previously used indicated   | Hold treatment until diastolic BP $\leq 90$ mmHg, and if symptomatic, until symptoms resolve. When treatment is restarted, continue at the same dose level.

If BP is not controlled with the addition of new or more intensive therapy, reduce by 1 dose level.

If Grade 3 hypertension recurs despite dose reduction and antihypertensive therapy, discontinue therapy

Anti-hypertensive therapy: Treat with the aim to achieve diastolic BP $\leq 90$ mmHg:
- Start anti-hypertensive medication AND/OR
- Increase current antihypertensive medication AND/OR
- Add additional anti-hypertensive medications. | Hold treatment until diastolic BP $\leq 90$ mmHg, and if symptomatic, until symptoms resolve. When treatment is restarted, continue at the same dose level. |
| Grade 4 : Life-threatening consequences (eg, malignant hypertension, transient or permanent neurologic deficit, hypertensive crisis)                         | Discontinue therapy                                                                                                                                                                                                                                                                                                                                                                                                                                                                                                                                                                                                                           | No dose modification                                                                                                                                        |

a For cohort [A], regorafenib should be interrupted and no dose reduction are allowed. Patients requiring a delay of > 4 weeks should permanently discontinue regorafenib

| ALT and/or AST and/or bilirubin increases related                                    | Regorafeniba
Management/Dose-modification                                                                                                                                                                                                                                                                                    | Avelumab
Management/Dose-modification                                                                                                                                                                                                                                                                                                                                                                                                                                                 |
|---------------------------------------------------------------------------------------------|---------------------------------------------------------------------------------------------------------------------------------------------------------------------------------------------------------------------------------------------------------------------------------------------------------------------------------------------------|-------------------------------------------------------------------------------------------------------------------------------------------------------------------------------------------------------------------------------------------------------------------------------------------------------------------------------------------------------------------------------------------------------------------------------------------------------------------------------------------------|
| < 3 times upper limit of normal (ULN) for ALT/AST and/or total bilirubin > ULN to 1.5 x ULN | Any occurrence
Continue Regorafenib treatment.
Monitor liver function weekly until transaminases return to <3 times ULN or baseline                                                                                                                                                                                                         | Continue Avelumab therapy.
Continue liver function monitoring
If worsens:
Treat as appropriated ALT/AST increased (see below)                                                                                                                                                                                                                                                                                                                                                          |
| AST or ALT > 3.0 to ≤ 5 x ULN
and/or total bilirubin > 1.5 to ≤ 3 x ULN                  |                                                                                                                                                                                                                                                                                                                                                   | Withhold Avelumab therapy

Increase frequency of monitoring to every 3 days
If returns to <3 times ULN or baseline: resume routine monitoring, resume Avelumab therapy
If elevation persists > 5-7 days or worsens : treat as appropriated ALT/AST increased (see below)                                                                                                                                                                                                            |
| AST or ALT > 5 x ULN to ≤20 x ULN and/or total bilirubin > 3 x ULN to ≤ 10 x ULN            | 1st occurrence :
Interrupt Regorafenib treatment.
Monitor transaminases weekly until return to <3 times ULN or baseline.
Restart: If the potential benefit outweighs the risk of hepatotoxicity, decrease dose by one dose level, and monitor liver function weekly for at least 4 weeks.

Re-occurrence : Discontinue permanently | discontinue Avelumab therapy

Increase frequency of monitoring to every 1 to 2 days
1 to 2 mg/kg/day prednisolone or equivalent

Add prophylactic antibiotics for opportunistic infections
Consult gastroenterologist / hepatologist
Consider obtaining MRI/CT scan of liver and liver biopsy if clinically warranted

If returns to <3 times ULN or baseline:
Taper steroids over at least 1 month
If does not improve in > 3 to 5 days, worsens or rebounds: |
| >20 times ULN
or >3 times ULN with concurrent bilirubin > 2 times ULN                    | Any occurrence
Discontinue permanently
Monitor liver function weekly until resolution or return to baseline.                                                                                                                                                                                                                                | Add mycophenolate mofetil 1 gram (g) twice daily
If no response within an additional 3 to 5 days , consider other immunosuppressants per local guidelines
Re-occurrence : Discontinue permanently                                                                                                                                                                                                                                                                                         |

a For cohort [A], regorafenib should be interrupted and no dose reduction are allowed. Patients requiring a delay of > 4 weeks should permanently discontinue regorafenib

| Diarrhea/colitis (NCI-CTCAE v5.0)                                                                                                                                                                                                                                 | Regorafenib a                                                                                                                                        | Avelumab                                                                                                                                                                                                                    |                                                                                                                                                                                                                                                                                                                                                      |
|-------------------------------------------------------------------------------------------------------------------------------------------------------------------------------------------------------------------------------------------------------------------|-----------------------------------------------------------------------------------------------------------------------------------------------------------------|-----------------------------------------------------------------------------------------------------------------------------------------------------------------------------------------------------------------------------|------------------------------------------------------------------------------------------------------------------------------------------------------------------------------------------------------------------------------------------------------------------------------------------------------------------------------------------------------|
|                                                                                                                                                                                                                                                                   |                                                                                                                                                                 | Initial Management                                                                                                                                                                                                          | Follow up Management                                                                                                                                                                                                                                                                                                                                 |
| Grade 1
Diarrhea: < 4 stools/day over baseline
Colitis: asymptomatic                                                                                                                                                                                        | No change                                                                                                                                                       | Continue Avelumab therapy
Symptomatic treatment (e.g. loperamide)                                                                                                                                                        | Close monitoring
Subject education
If worsens: treat as grade 2, 3 or 4                                                                                                                                                                                                                                                                        |
| Grade 2
Diarrhea: 4 to 6 stools per day over baseline; IV fluids < 24h; not interfering with ADL
Colitis: abdominal pain; blood in stool                                                                                                                    | No change                                                                                                                                                       | Withhold Avelumab therapy
Symptomatic treatment                                                                                                                                                                          | If improves ≤ grade 1: Resume Avelumab therapy
If persists >5-7 days or recurs, treat as grade 3 or 4                                                                                                                                                                                                                                             |
| Grade 3 to 4
Diarrhea (Grade 3): ≥ 7 stools per day over Baseline; incontinence; IV fluids ≥ 24h; interfering with ADL
Colitis (grade 3): severe abdominal pain, medical intervention indicated, peritoneal signs
Grade 4: life-threatening, perforation | Delay until ≤ grade 2 and reduce 1 dose level for grade 3

Permanently discontinue for grade 4, recurrent grade 3 or in case of no recovery after 4 weeks | Withhold for grade 3

Permanently discontinue for grade 4 or recurrent grade 3
1.0 to 2.0 mg/kg/day prednisone or equivalent add prophylactic antibiotics for opportunistic infections
Consider lower endoscopy | If improves:
Continue steroids until grade ≤1, then taper over at least 1 month; resume Avelumab therapy following steroids taper (for initial Grade 3).

If worsens persists > 3 to 5 days, or recur after improvement:
Add infliximab 5mg/kg (if no contraindication),
Note: infliximab should not be used if perforation or sepsis |

a For cohort [A'], regorafenib should be interrupted and no dose reduction are allowed. Patients requiring a delay of > 4 weeks should permanently discontinue regorafenib

| Rash (NCI-CTCAE v5.0)                                                                               | Regorafenib a                                                                                                                                                                                                                                                                                                                                                                                                                    | Avelumab                                                                                                                                                                                                                                                            |                                                                                                                                                                                                                                                                                                                                                                                                |
|-----------------------------------------------------------------------------------------------------|---------------------------------------------------------------------------------------------------------------------------------------------------------------------------------------------------------------------------------------------------------------------------------------------------------------------------------------------------------------------------------------------------------------------------------------------|---------------------------------------------------------------------------------------------------------------------------------------------------------------------------------------------------------------------------------------------------------------------|------------------------------------------------------------------------------------------------------------------------------------------------------------------------------------------------------------------------------------------------------------------------------------------------------------------------------------------------------------------------------------------------|
|                                                                                                     |                                                                                                                                                                                                                                                                                                                                                                                                                                             | Initial Management                                                                                                                                                                                                                                                  | Follow up Management                                                                                                                                                                                                                                                                                                                                                                           |
| Grade 1 to 2
Covering ≤ 30% body surface area                                                    | 
No change
 
Consider skin biopsy and dermatology consult
 
Consider 1.0 mg/kg/day prednisone or equivalent (max 1 week, taper steroids included) and/or dermocorticoids
 
In case of fever, consider infectious etiology in case of pruritus, add antihistamine
                                                                                                                                                       | Continue avelumab therapy
Symptomatic therapy (for example, antihistamines, topical steroids)                                                                                                                                                                    | 
If Grade 2 persists > 1 to 2 weeks or recurs:
Withhold Avelumab therapy
Consider skin biopsy
Consider 0.5 - 1.0 mg/kg/day prednisone IV or equivalent
One improving, taper steroids over at least 1 month, consider prophylactic antibiotics for opportunistic infections, and resume Avelumab therapy following steroid tapers
If worsen: treat as grade 3 to 4
 |
